### Proposed sample size/Power calculations

The primary hypothesis is that the damage control principle is able to reduce the extent of organ failure. Organ failure is measured daily by the SOFA score (five organs, excluding CNS, 0-4 points per organ). The maximum SOFA score during ICU stay is used as primary outcome measure. It is assumed that the maximum SOFA score could be reduced by 1-2 points. This corresponds to a reduction from "organ failure" to "organ dysfunction", or from "organ dysfunction" to "normal organ function" for one organ. Data from Ferreira et al. indicate that a 2 point increase in SOFA score correlates with an average 10% increase in mortality [29]. According to the database of the Deutsche Interdisziplinäre Vereinigung Intensivmedizin (DIVI; quality assessment in intensive care; 45.000 admissions 2000-2004) maximum SOFA score is about 3.2 ± 3.2 in a general ICU population, and 3.3 ± 3.1 in emergency admissions with trauma. Thus the estimated effect (1.5 points reduction) corresponds to a standardized effect size of 0.5. Assuming usual error rates (a = 0.05; b = 0.20), 64 patients per group would be required. However, due to the non-normal nature of the distribution and the use of non-parametric statistics, the number of patients to be randomized has to be increased by 10%. Thus, the total sample size is set to 140 patients (70 per group). Compliance and rate of loss to follow-up do not affect primary outcome measures.

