### Statistical analyses

The main outcome variable is the maximum SOFA score during ICU stay. In order to have comparable periods, the time period for SOFA score assessment is limited to the first 28 days after trauma. Documentation of daily SOFA scores is continued in intermediate care or other high dependency units.

The maximum SOFA score will be compared using non-parametric statistics (U-test) due to the substantial skewness of the distribution. Since severity of trauma is assumed to be a major determinant of outcome (including rate of organ failure) the comparability regarding Injury Severity Score (ISS) is tested before analysis. In case of substantial imbalance (p < 0.15; U-test) a stratified analysis of outcome will be performed (two groups; ISS ≤/> 30 points).

Analysis will be done according to intention to treat; regarding to the per protocol (PP) analysis we expect the PP-population to be 5% less.

There will be one interim analysis of data collection when about half of the expected sample size has been included (70 cases). The p-value for the interim analysis will be set at 0.005 so that the final analysis will be done at a significance level of 0.048, according to Fleming and O'Brien [31].

During interim and final analysis, a detailed safety analysis will be performed by comparing predicted and observed survival within each group and reviewing individual cases of non-survivors.

In addition, all secondary endpoints mentioned in the protocol will be considered for explorative analysis, because these factors are repeatedly named in the discussion about the advantages of damage control orthopedics. The aim of presenting all these data is not a confirmative statistical testing, but rather to serve as a basis for comparative analyses in future meta-analyses regarding damage control orthopedics versus early total care strategies.

The hospital perspective on costs includes the initial and all secondary operations or readmissions until one year after randomization. As most costs during hospital stay are caused by surgery itself and ICU care, data collection and statistical analysis will focus on these two aspects. The results will be reported as a cost-effectiveness analysis using life-years lost as the measure of treatment benefit. These analyses will employ decision-analytic models for the optimum management of multiply injured patients with femoral shaft fracture.

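### The quoted trauma SD makes a 1.5-point reduction an effect of 0.48, not 0.5, so 140 patients give about 77-78% power by the plan's own method, not 80%

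*Protocol article*

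**What the plan says.** The section on sample size and power in the protocol article gives the whole derivation.

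- Effect: "It is assumed that the maximum SOFA score could be reduced by 1-2 points". The figure carried forward is 1.5 points, the middle of that range.
- Spread, from an intensive care quality database: "maximum SOFA score is about 3.2 ± 3.2 in a general ICU population, and 3.3 ± 3.1 in emergency admissions with trauma".
- Standardization: "Thus the estimated effect (1.5 points reduction) corresponds to a standardized effect size of 0.5".
- Base size: "Assuming usual error rates (a = 0.05; b = 0.20), 64 patients per group would be required".
- Allowance for the non-normal distribution and the non-parametric test: "the number of patients to be randomized has to be increased by 10" per cent, which leads to 70 per group and 140 in total.

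The section on statistical analyses names the U-test as the primary test. It sets one interim analysis at about 70 cases with a p-value of 0.005, after which "the final analysis will be done at a significance level of 0.048". The sample size section works at 0.05 and does not mention the interim look.

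**The concern.** The standardized effect is presented as following from the SDs in the preceding sentence, but neither SD produces 0.5. Required sample size varies with the inverse square of the effect, so a small upward rounding matters: the base size is 64 per group at 0.5, but 69 at SD 3.1 and 73 at SD 3.2 (two-sided 0.05, 80% power). These increases of 8% and 14% are of the same order as the 10% that the plan itself added for the U-test.

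What is at stake is how a non-significant result would be read. A reader would take the type II error for a 1.5-point reduction to be 0.20, whereas the plan's own inputs give more. The article's discussion also contemplates a conclusion of non-inferiority for primary internal fixation, so the true type II error bears on interpretation.

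**Working it through.** **Inputs.** From the sample size section: difference 1.5 points; SD 3.1 (trauma) or 3.2 (general ICU); alpha 0.05; beta 0.20; 10% uplift; 70 per group. From the statistical analyses section: 0.005 at the interim look (about half the patients) and 0.048 at the end. The plan does not state sidedness. Two-sided is inferred because a one-sided 0.05 would give about 50 per group, not 64.

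**Step 1: reproduce the plan.** For a two-sample t-test (noncentral t) with d = 0.5, two-sided alpha 0.05 and 80% power, n = 64 per group. Then 64 × 1.10 = 70.4, set to 70. The plan's figures reproduce, but only with d = 0.5.

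**Step 2: standardize with the quoted SDs.** d = difference / SD.

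- Trauma: 1.5 / 3.1 = 0.484
- General ICU: 1.5 / 3.2 = 0.469
- SD needed for 0.5: 1.5 / 0.5 = 3.0, which the section does not quote

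**Step 3: effective size.** The plan says that the 10% pays for the U-test, so effective n = 70 / 1.10 = 63.6 per group.

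**Step 4: power at 63.6 per group.** The single-test columns use the noncentral t with df = 2n − 2 and noncentrality d × √(n/2). The both-looks column is the probability of rejecting at either analysis, from the bivariate normal with half the information at the interim (correlation √0.5).

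| SD | d | Single test, 0.05 | Final test alone, 0.048 | Both looks, 0.005 and 0.048 |
|---|---|---|---|---|
| 3.0 (not quoted) | 0.500 | 79.9% | 79.4% | 80.2% |
| 3.1 (trauma) | 0.484 | 77.3% | 76.8% | 77.6% |
| 3.2 (general ICU) | 0.469 | 74.7% | 74.1% | 75.0% |

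**Step 5: separate the causes.** In the top row the effect is held at 0.5 with 70 per group.

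- Rounding 70.4 to 70 leaves 79.9%.
- Testing at 0.048 costs 79.9 − 79.4 = 0.5 point if only the final test is counted. With interim rejections included, power is 80.2%.
- Moving down the table at alpha 0.05, the SD alone costs 79.9 − 77.3 = 2.6 points (3.1) or 79.9 − 74.7 = 5.2 points (3.2).

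**Step 6: size needed for 80% by the plan's method**, final test at 0.048.

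- SD 3.1: 69 × 1.10 = 75.9, so 76 per group (152 in total)
- SD 3.2: 74 × 1.10 = 81.4, so 82 per group (164 in total)

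**Step 7: effect detectable with 80% power at 63.6 effective per group.** d = 0.504 for the final test alone and 0.499 counting both looks, so about 0.50. In points, 0.50 × 3.1 = 1.55 and 0.50 × 3.2 = 1.60.

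**Step 8: sensitivity to the 10%.** Power is given for the final test alone, then for both looks.

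| Assumed loss from the U-test | SD 3.1 | SD 3.2 |
|---|---|---|
| Plan's 10% (63.6 effective) | 76.8%, 77.6% | 74.1%, 75.0% |
| Normal-theory efficiency 0.955 (70 × 0.955 = 66.9 effective) | 78.8%, 79.6% | 76.2%, 77.0% |
| No loss (70 effective) | 80.6%, 81.4% | 78.1%, 78.9% |

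**The case against.** The best defence is that this is rounding to one decimal in a calculation that is approximate throughout. The effect is a range of 1 to 2 points, the registry values are given as approximate, and 0.484 does round to 0.5. At SD 3.1 an effect of 0.5 means 1.55 points, only 0.05 point from the planning value on a 20-point integer score. Across the plan's own range, power at SD 3.1 (63.6 effective, 0.048) runs from 43% for 1 point to 95% for 2 points, which dwarfs a 3-point shift. This stands as a limit on importance. It does not make the stated figures agree, because the section commits to 1.5 points and a beta of 0.20.

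It can also be said that the 10% is a rule of thumb and that the U-test may lose less. That is fair. With the normal-theory efficiency and both looks counted, the trauma SD gives 79.6%, almost the stated value. But the plan says the increase is required by the distribution and the test, and by its own statement the 10% is not spare.

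A reader might infer a stronger charge: three favourable roundings acting together, with the 0.048 level and the step from 70.4 to 70 as causes alongside the effect size. The figures do not support this. At an effect of 0.5, with 70 per group and both looks counted, power is 80.2%. Nor is 74% the fair headline: it pairs the general-ICU SD with the final test alone, although the same sentence of the plan supplies a trauma SD that is closer to this trial.

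**Conclusion.** The point holds, at modest size. The plan's quoted SDs give a standardized effect of 0.48 (trauma) or 0.47 (general ICU), not 0.5. By the plan's own method, 140 patients have about 77-78% power for a 1.5-point reduction on the trauma SD and about 74-75% on the general-ICU SD. The stated type II error of 0.20 is therefore about 0.22-0.23, or 0.25-0.26 on the less relevant SD. Rounding the effect size is the only material cause.

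The result rests on three assumptions: a two-sided test, normal-theory power as the plan used it, and the plan's statement that the 10% is consumed by the non-parametric test. It also takes the registry SDs as given. Whether they suit patients with a 20-60% predicted probability of death, with deaths scored at 20, is a separate question that this calculation does not address. The corrected power should not be read as a forecast for the trial population.

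**What to change.** Keep 140 patients and correct the sample size section in one of two ways.

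- State the standardized effect as about 0.48 for 1.5 points at the trauma SD of 3.1, and the power as about 77% (about 75% if the SD is 3.2), noting that the final test is at 0.048 after an interim look at 0.005.
- Or state what the sample size does deliver: 70 per group, after the 10% allowance, has 80% power for about 0.50 SD, that is about 1.55-1.6 points at SDs of 3.1-3.2.

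Either version should say that the figures take the registry SDs as given. The cost is wording only, with a slightly less favourable power figure. Recruitment, design and analysis are unchanged. Restoring 80% power for 1.5 points on the quoted SDs would instead need about 152-164 patients by the same method, but the size of the shortfall does not by itself require that.

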### Feasibility of recruitment

According to the Trauma Registry of the DGU (1993 - 2004, n = 20.815), 12% of multiple trauma cases had a fracture of the femoral shaft. The limitation to patients with ISS ≥ 16 does not change this rate. A level 1 trauma center treats 50-100 severe trauma patients each year (as observed in the German Trauma Registry). Thus, 15 participating centers will be able to screen at least 1000 patients per year. The number of appropriate patients with femur shaft fractures is 6 - 12 per year per center. Regarding the fact that not every case could be included due to organisational difficulties, only about half of these cases will be included and randomized.

### Statistical analyses

The main outcome variable is the maximum SOFA score during ICU stay. In order to have comparable periods, the time period for SOFA score assessment is limited to the first 28 days after trauma. Documentation of daily SOFA scores is continued in intermediate care or other high dependency units.

The maximum SOFA score will be compared using non-parametric statistics (U-test) due to the substantial skewness of the distribution. Since severity of trauma is assumed to be a major determinant of outcome (including rate of organ failure) the comparability regarding Injury Severity Score (ISS) is tested before analysis. In case of substantial imbalance (p < 0.15; U-test) a stratified analysis of outcome will be performed (two groups; ISS ≤/> 30 points).

Analysis will be done according to intention to treat; regarding to the per protocol (PP) analysis we expect the PP-population to be 5% less.

There will be one interim analysis of data collection when about half of the expected sample size has been included (70 cases). The p-value for the interim analysis will be set at 0.005 so that the final analysis will be done at a significance level of 0.048, according to Fleming and O'Brien [31].

During interim and final analysis, a detailed safety analysis will be performed by comparing predicted and observed survival within each group and reviewing individual cases of non-survivors.

In addition, all secondary endpoints mentioned in the protocol will be considered for explorative analysis, because these factors are repeatedly named in the discussion about the advantages of damage control orthopedics. The aim of presenting all these data is not a confirmative statistical testing, but rather to serve as a basis for comparative analyses in future meta-analyses regarding damage control orthopedics versus early total care strategies.

The hospital perspective on costs includes the initial and all secondary operations or readmissions until one year after randomization. As most costs during hospital stay are caused by surgery itself and ICU care, data collection and statistical analysis will focus on these two aspects. The results will be reported as a cost-effectiveness analysis using life-years lost as the measure of treatment benefit. These analyses will employ decision-analytic models for the optimum management of multiply injured patients with femoral shaft fracture.

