### Reasoning for inclusion and exclusion criteria

The inclusion of patients with multiple trauma and corresponding fractures arises from the question of the study itself. Patients with thoracic or cranial trauma will be included according to systematic review of literature.

As patients might be randomized into the group "primary definitive surgery", patients in whom this procedure is not feasible or can not be performed (begin of surgery not within 24 hours possible or different procedure initiated) must be excluded.

The calculation of the probability of death with the given formula (see below) is a validated method of estimating the probability of death in multiple trauma patients [23-25]. It is essential though that all parameters entered are present at the time of calculation. Patients with missing values that are needed can not be included into the study.

Considering probability of death at randomization will allow an equal distribution of global prognosis in both treatment arms. Because the most important factors that determine prognosis in multiple trauma patients are considered, a comparison of this heterogenic patient collective is possible.

Open fractures are not an exclusion criteria per se [26]. Only III° open fractures will be excluded from this study as many surgeons do not favour the option of nailing in such severe open fractures [27,28].

Patients included in or about to be included in other interventional trials or trials involving drugs of any kind must be excluded out of judicial and scientific reasons.

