### Method of assigning patients to treatment groups

All multiple trauma patients with femur shaft fractures and age > or = 18 years that present to the involved hospitals will be recorded and eligibility will be checked. The probability of death will be calculated on the trial website using clinical data as described below. If all inclusion criteria are fulfilled the patient will be randomized and documentation will be started (figure 1). Reasons for non-inclusions must be recorded. Allocation concealment will be guaranteed by internet randomization where patients have to be named before allocation to one of the therapy arms. The validated system for internet randomization will be provided by the Coordinating Center for Clinical Studies Cologne (KKSK). This system generates the allocation sequence as follows: The randomisation sequence is blocked using varying block sizes between 6 and 10. Furthermore, randomisation is stratified by study center, in order to adjust for center-specific variation in treatment routines.

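### Whether maximum SOFA is adjusted for trauma severity depends on a baseline significance test of ISS; naming one severity-adjusted primary analysis in advance is a free improvement

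*Protocol article*

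**What the plan says.** All of the rule stands in the Statistical analyses section of the protocol article.

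- Default comparison: "The maximum SOFA score will be compared using non-parametric statistics (U-test) due to the substantial skewness of the distribution".
- Role of severity: "severity of trauma is assumed to be a major determinant of outcome".
- Pre-test: "the comparability regarding Injury Severity Score (ISS) is tested before analysis".
- Consequence: "In case of substantial imbalance (p < 0.15; U-test) a stratified analysis of outcome will be performed", with strata given as "two groups; ISS ≤/> 30 points".

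The section does not state whether the stratified result then becomes the primary result or is reported beside the U-test.

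Two other places bear on this. Under Method of assigning patients to treatment groups, "randomisation is stratified by study center, in order to adjust for center-specific variation in treatment routines"; no severity measure is named as a stratification factor. Under Reasoning for inclusion and exclusion criteria, the text expects balance all the same: "Considering probability of death at randomization will allow an equal distribution of global prognosis in both treatment arms". Other baseline characteristics mentions adjustment only with the RISC score, and only as exploratory.

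**The concern.** A baseline significance test asks whether an ISS difference arose by chance. In a properly randomised trial it did, so the p-value answers no useful question. What makes adjustment worthwhile is how strongly ISS predicts maximum SOFA, and the p-value says nothing about that.

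Making adjustment conditional on the test has three consequences:

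- The form of the analysis is settled only after data are seen.
- In the triggered trials it is unclear which p-value is confirmatory.
- In most trials a covariate that the protocol considers strongly prognostic is left unused. The trial was planned for only 80% power.

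**Working it through.** **The plan's own figure.** Inputs from Proposed sample size/Power calculations: standardised effect 0.5, α 0.05 (two-sided assumed), power 80%. A two-sample t-test needs 63.8, so 64 per group. 64 × 1.10 = 70.4, so 70 per group and 140 in total. The figure reproduces and is not in dispute.

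**How often the rule fires, and what it lets through.** With 70 per arm, the difference in mean ISS has standard error √(2/70) = 0.169 SD under randomisation.

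- By construction the pre-test gives p < 0.15 in 15% of trials (14.3–15.0% in the simulated null trials below). About 85% are not adjusted.
- The threshold is about 1.44 × 0.169 = 0.243 SD. Larger imbalances are nearly always flagged.
- Imbalance above 0.1 SD: 0.1/0.169 = 0.59, two-sided probability about 55%. Subtracting the 15% flagged leaves about 40% of all trials (40/55 ≈ 73% of those above 0.1 SD).
- Imbalance above 0.2 SD: 23–24% of trials, of which about 40% are unflagged in simulation.
- Largest outcome shift left in an unflagged trial = ρ × 0.243 SD, where ρ is the ISS–outcome correlation. With an outcome SD of 3.0 this is 0.22, 0.36 and 0.51 SOFA points at ρ = 0.3, 0.5 and 0.7. The planned effect is 1.5 points.

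**Type I error and power.** ρ is not in the documents, so a range is shown. Simulation: 8,000 trials per setting, 70 per arm, a skewed integer outcome on 0–20 (control mean about 3.1, SD about 3.0), effect 0.5, two-sided level 0.048. The two-stage rule is simulated as a stratified rank test (van Elteren) replacing the U-test when the pre-test fires. Strata are split at the ISS median, because the documents do not give the ISS distribution. Monte Carlo standard error is about 0.4 points for power and 0.24 points for type I error.

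| ρ | Type I error, two-stage | Power: plain U | Two-stage | Always stratified | Rank ANCOVA on ISS |
|---|---|---|---|---|---|
| 0 | 4.5% | 79.3% | 79.3% | 79.0% | 79.4% |
| 0.3 | 4.4% | 79.5% | 80.2% | 81.3% | 82.6% |
| 0.5 | 3.7% | 79.3% | 81.0% | 85.5% | 88.5% |
| 0.7 | 3.0% | 80.2% | 84.1% | 91.8% | 96.7% |

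Gain of continuous adjustment over the two-stage rule: 0.1, about 2.5, about 7.5 and about 12.6 points at ρ = 0, 0.3, 0.5 and 0.7.

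**Sensitivity to deaths scored at 20.** A separate simulation assumed 35% of patients scored 20, ISS about N(34, 11) clipped to 16–75, and the actual cut at 30. It gave 70–72% (two-stage) against 73–74% (adjusted) at ρ = 0.3, and 71–72% against 80–81% at 0.5. Type I error of the rule was 3.3–4.7%. A further check with about 35% of controls at 20 gave 80% against 82%, and 81% against 88%. Together these give losses of roughly 2–3 points at 0.3 and 7–9 points at 0.5.

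**The case against.** **The unadjusted trials are the better-balanced ones.** A reader might infer that real imbalance goes uncorrected in most trials. The arithmetic does not support that: unflagged imbalance is capped near 0.24 SD, about 60% of trials above 0.2 SD are caught, and the share with an unadjusted imbalance above 0.1 SD is about 40%, not a majority.

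**False positives.** A reader might also infer that trials just above the threshold keep a biased test. Among trials with an ISS p-value of 0.15–0.20, the U-test's error rate is about 7% at ρ = 0.5, but only about 5.7% at 0.3 and 4.9% at 0.1. That band holds about 5% of trials. Over all unflagged trials the error is below nominal (4.3% at 0.3, 3.5% at 0.5), and the rule as a whole is conservative.

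**The correlation may be small.** Eligibility requires a calculated death risk of 20–60%, from a formula that already contains ISS. Inside that window a high ISS tends to be offset by better values elsewhere. A generic check assumed normal predictors, a logit SD of 1.5–2.5, ISS carrying 20–40% of the score variance, and an outcome driven only through the score. Correlations of 0.31–0.57 fell to 0.02–0.15. This shows direction, not size: if ISS affects organ failure beyond the score, the correlation is higher. The point stands as a reason not to promise a large gain.

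**The stratified analysis may be only supplementary.** The text allows that reading, and the primary test would then be fixed. But the plain U-test has no more power than the two-stage rule (79.5% and 79.3% at ρ = 0.3 and 0.5), so the loss remains, and the ambiguity is itself a defect.

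**The cut at 30.** It would be too strong to say that two groups throw away most of the information. At ρ = 0.5, always stratifying recovers (85.5 − 81.0)/(88.5 − 81.0) = 60% of the gain; at 0.3 it recovers just under half. The main problem is the condition, not the cut.

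**This is a condensed article.** That would excuse missing detail. Here a rule is stated, and the rule itself is the problem.

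**Conclusion.** The point holds as a free improvement. The article makes severity adjustment of the primary endpoint conditional on a test that detects only chance imbalance, and leaves open which result is primary when the test fires. About 85% of trials would go unadjusted, with a bounded imbalance.

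There is no inflation of type I error: about 3 to 4.7% against 4.8%. The cost is an analysis that depends on the data, conservatism, and lost power of about 0, 2–3 and 7–9 points at correlations of 0, 0.3 and 0.5.

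These sizes rest on an assumed ISS–outcome correlation and assumed outcome and ISS distributions. The low end is plausible given the eligibility window. Even there, unconditional adjustment cost no power in the simulation (79.4% against 79.3% at zero correlation) and its type I error stayed close to nominal. Randomisation does not remove the need: as described, it is stratified by centre only.

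**What to change.** Delete the ISS pre-test. Name in advance one primary analysis of maximum SOFA that accounts for severity whatever the observed imbalance. Suitable choices are rank ANCOVA or a proportional-odds model with treatment and continuous ISS or calculated probability of death; the minimum is a van Elteren test always stratified by ISS. State that this result is primary and that the plain U-test is a sensitivity analysis.

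The cost is a wording change in the protocol and SAP, made before any comparative data are seen. No new data are needed: ISS and the other components of the death-risk formula must be known for a patient to be included, so the covariate will not be missing. The sample size need not change.
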